##### Mixed Method Integration

We will merge qualitative and quantitative databases for analysis and interpretation. Specifically, we will use a joint display of data to visually represent and compare findings from each data set as they relate to key concepts [77,78,81]. We will be attentive to differences in the ethnoracial composition of the data sets to identify any themes that are unique to non-Black, non-Latino/a/x people of color. Implications for the measurement of divergent or inconsistent findings will be identified, with particular attention to how optimal measurement strategies might differ across intersectional groups and research foci.

### Sample Size

For cognitive interviews, our sample size exceeds qualitative research guidelines for achieving data saturation—the number of interviews by which no new relevant themes are identified (eg, up to 25 participants) [82,83]. The quantitative survey sample sizes were determined based on sample size requirements for multigroup CFA, which has the greatest sample size requirement among the planned analyses. Simulation studies show that 200 respondents per group is the minimum number required to have ≥80% power to detect measurement invariance via changes of ≥0.002 in the comparative fit index [75]. Therefore, we will recruit 250 per race and ethnicity*SGM*gender stratum in English (n=3000); the Spanish-language sample (n=500) will allow for mCFA by language as well as by SGM status, race, or gender. All other planned quantitative analyses have smaller sample size requirements.

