### Participants

Eligible participants will be aged ≥18 years and residing in the United States. For cognitive interviews (25/50, 50% English; 25/50, 50% Spanish), participants will be of any race and ethnicity and purposively sampled to achieve maximum diversity in gender, sexual orientation, race and ethnicity, socioeconomic status, age, and nativity. Quota sampling will be used for the quantitative surveys. The Spanish survey (n=500) will include 250 SGM and 250 non-SGM. The English survey (n=3000) will include non-Hispanic Black (1000/3000, 33%), non-Hispanic White (1000/3000, 33%), and Hispanic or Latino/a/x persons of any race (1000/3000, 33%), with 50% (250/500 for Spanish and 1500/3000 for English) of each group being composed of SGM. We will further stratify recruitment by gender to generate sample sizes of approximately 250 at each race and ethnicity *SGM* gender intersection (eg, White non-SGM women). Transgender and gender nonbinary respondents will be grouped by gender identity (eg, transgender men and transmasculine persons with men).

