#### Intersectional Discrimination Index

All Spanish-language participants will receive the unattributed InDI (Multimedia Appendix 1), with potential modifications based on cognitive interview findings. For the English survey, we will use the block-randomization feature in Qualtrics to implement a split-ballot design: 1000 participants will receive each of the unattributed, item-level attributed, or overall attributed versions of the InDI.

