#### Aim 2: Psychometric Evaluation of the InDI Measures Across Languages and Intersecting SSPs

Analyses will be conducted in MPlus (Muthén & Muthén) and Stata (StataCorp LLC). As a first step, we will conduct exploratory factor analysis, exploratory structural equation modeling, and confirmatory factor analysis (CFA) of the InDI-D and InDI-M in our previously collected data, using split-halves of the sample by country (n=1065 and n=1518). These analyses will help us establish the configural and metric structures of the two enacted discrimination measures. We previously used this approach to assess the psychometric properties of the InDI-A, finding support for its hypothesized unidimensionality. At that time, we opted not to conduct factor analyses of the enacted discrimination measures, with the rationale that their items are causal-formative indicators that aggregate to form a construct, rather than items that reflect the level of an underlying construct and should necessarily correlate [69]. Nevertheless, existing research demonstrates that discrimination scales do show strong interitem correlations and factor structures [47], likely reflecting both respondent characteristics that determine perception and self-reporting of discrimination, as well as the social clustering of discrimination. Furthermore, the assessment of configural, metric, and scalar structures of the InDI measures should precede the evaluation of measurement equivalence across intersectional groups, thereby determining whether the discrimination burdens they estimate can be meaningfully compared across groups [47]. We will evaluate the goodness of fit for CFA with parsimony, incremental, and absolute indices [70]. If substantive changes are made to the InDI items in aim 1, we will instead conduct the exploratory factor analysis, exploratory/confirmatory factor analysis, and CFA using randomly selected samples of the new survey data (n=200 each).

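### The 250 per stratum meets the plan's own 200-per-group minimum only if three questionnaire versions are pooled, which the plan neither states nor tests; on one version a stratum has about 83

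*Protocol article*

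**What the plan says.** The Sample Size section rests the survey size on multigroup CFA (mCFA), described as the most demanding planned analysis. It states that "200 respondents per group is the minimum number required to have ≥80% power", with power defined for changes of at least 0.002 in the comparative fit index (CFI). From this it concludes "we will recruit 250 per race and ethnicity*SGM*gender stratum in English (n=3000").

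The Intersectional Discrimination Index subsection under Quantitative Surveys describes a split-ballot design for that same English sample: "1000 participants will receive each of the unattributed, item-level attributed, or overall attributed versions of the InDI". All Spanish respondents receive the unattributed version.

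The Aim 2 analysis plan runs mCFA on the new survey data by language and across the 12 strata. It does not say whether the three English versions are pooled or analysed separately. The MIMIC covariates listed are gender, sexual orientation, race and ethnicity, socioeconomic status, age and nativity.

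For the Spanish survey, the Sample Size section says that n=500 "will allow for mCFA by language as well as by SGM status, race, or gender". The Participants section gives the split as "The Spanish survey (n=500) will include 250 SGM and 250 non-SGM". The footnote to Table 1 states that both language samples use quotas by race and ethnicity as well as by sexual or gender minority (SGM) status.

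**The concern.** The 250 per stratum counts people who answered three different forms of the instrument. It counts as one group of 250 only if the forms measure the same thing in the same way.

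The protocol does not take that for granted. The Introduction's section on attribution reports the argument that attributed and unattributed measures tap different constructs, and says that no study has tested it. Aim 3 exists to decide whether attributions belong in the measures.

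Aim 2 itself says that equivalence of all scale structures is needed before groups can be meaningfully compared. That standard is applied to language and strata but not to version. The only planned check on version is Aim 3's comparison of mean or median scores. Equal means do not show equal loadings or thresholds.

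At stake is what the Aim 2 result describes. If Aim 3 recommends the unattributed form, 2000 of the 3000 English respondents behind the 12-stratum verdict will have answered some other form.

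**Working it through.** **Inputs**
- Minimum 200 per group for at least 80% power; 250 per stratum; English n=3000 (Sample Size).
- 12 strata: 3 race and ethnicity × 2 SGM status × 2 gender (Participants; Aim 2).
- 1000 English respondents per version; Spanish unattributed only (Intersectional Discrimination Index subsection).
- Spanish n=500, 250 SGM and 250 non-SGM (Participants).

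**The plan's own figure.** 3 × 2 × 2 = 12 strata and 12 × 250 = 3000, which reproduces. The 80% power at 200 per group comes from a cited simulation. Its model size, loadings and degree of non-invariance are not given, so that figure cannot be reproduced.

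**Stratum size by version**
- One version: 1000/12 = 83.3, and 83.3/200 = 42% of the minimum.
- Spread, if version is allocated without regard to stratum: SD = √(250 × 1/3 × 2/3 × 2750/2999) ≈ 7.1, giving a 95% range of about 69 to 97.
- Two attributed versions pooled: 2 × 83.3 = 167, below 200.
- All three pooled: 250, above 200.
- English sample needed for 200 per stratum in every version: 200 × 12 × 3 = 7200.

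**Illustration of power (assumptions, not the cited simulation).** Take a chi-square test at alpha 0.05, set its noncentrality to give 80% power at 200 per group, and scale it by n/200. With 1 df and n = 83.33, power = Φ[(1.960 + 0.842) × √(83.33/200) − 1.960] = Φ(−0.15) = 44%. Over a range of degrees of freedom:

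| df | n = 83 | n = 167 | n = 250 |
|---|---|---|---|
| 1 | 44% | 72% | 88% |
| 5 | 39% | 71% | 89% |
| 20 | 35% | 70% | 90% |
| 88 | 31% | 69% | 91% |

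The plan decides by change in CFI and not by a chi-square test, so these values show direction and rough scale only.

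**Groupings that reach 200 within one version**
- Race and ethnicity: 1000/3 = 333.
- SGM × gender: 1000/4 = 250.
- Race and ethnicity crossed with either SGM status or gender: 1000/6 = 167, which does not.

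**Language comparison.** Like for like, this is 1000 English unattributed against 500 Spanish unattributed. Both exceed 200.

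**Spanish subgroups.** SGM status gives 250 against 250, which is adequate. For race or gender, each group needs 200/500 = 40% of the sample. Three groups would need 600, more than the 500 planned.

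**The case against.** The strongest reply is that the plan implies pooling. It uses the new survey data without restriction, across strata sized at 250, and 250 exceeds 200. Version is randomised, so its mix is similar in every stratum and pooling does not confound version with stratum. The plan also has other tools: MIMIC models on the full sample, partial invariance and the alignment method. The article is condensed, and the full plan may define the analysis set.

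Much of this stands. A reader might infer that the stated power is simply not delivered. The documents do not support that, because the shortfall arises only if the mCFA is run within one version, and no section plans that.

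Two other stronger readings also fail:
- If Aim 1 changes items, the preliminary factor analyses are to be done "using randomly selected samples of the new survey data (n=200 each"). A reader might take this as a breach of the minimum. Even if three separate English samples are held out, (3000 − 600)/12 = 200 per pooled stratum remain, which is exactly the minimum.
- A reader of the Participants section alone might conclude that the Spanish survey has an SGM quota only. Table 1's footnote says otherwise, so this is a conflict to reconcile and not an established absence.

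What the reply does not answer is that pooling assumes the version equivalence that the study treats as unknown. Randomisation balances the forms across strata, but it does not make a verdict on the mixture apply to the one form recommended. Nor is this only omitted detail, since the sample-size conclusion and the three-way split are both fixed in this article.

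**Conclusion.** The concern holds in a limited form. The 250 per stratum, and the power basis attached to it, apply only to the three versions pooled. For any single version the 12-stratum comparison has about 83 per group, 42% of the plan's minimum, and the stated power basis does not extend to it. The pooling is unstated, and no planned analysis tests whether loadings or thresholds are the same across versions.

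The group sizes are simple arithmetic on the plan's figures; the range of 69 to 97 assumes allocation without stratification. The actual power at 83 cannot be derived from the document, and 31–44% is an illustration under the assumptions stated. The shortfall concerns the 12-stratum mCFA and not the language comparison. The Spanish claim of mCFA by race or gender is not secured by any group sizes given, and the quota descriptions disagree.

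**What to change.** 1. **Sample Size.** State that 250 per stratum and the power basis refer to the three versions pooled, and that a single version gives about 83 per stratum, below the 200 minimum.
2. **Aim 2.** Before the 12-stratum analysis, run a three-group mCFA by version (1000 each) using the CFI criterion already chosen, and add version as a MIMIC covariate. Pool only if equivalence holds. If it does not, report the unattributed arm in groupings that still reach 200 (race and ethnicity, about 333 each, or SGM × gender, about 250 each), and state that any 12-stratum result for one form is below the minimum. The version analysis would also test directly the construct question raised in the Introduction, which the score comparison in Aim 3 cannot.
3. **Spanish survey.** Reconcile Table 1's footnote with the Participants section, and limit the claim of mCFA by race or gender to groups that actually reach 200.

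The cost is one additional analysis, one model term and some rewording, with no added participants. The stated power becomes less favourable. If versions prove non-equivalent, the fallback groupings give up the full three-way intersection at the stated power.

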## Results

The study was funded by the National Institute on Minority Health and Health Disparities from May 6, 2021, to January 31, 2023 (Multimedia Appendix 2). The study was approved by the institutional review board of Drexel University in May 2021 (IRB # 2006007889). Cognitive interview data collection began in July 2021. The publication of study results is expected to begin in early 2023.

## Discussion

### Study Importance

This study offers multiple innovations. It aligns with the National Institute on Minority Health and Health Disparities priorities for promoting the advancement of health disparities science by “strengthen[ing] the understanding of how racism and discrimination are conceptualized and measured, and how they contribute to health disparities” [84]. The key deliverables of this study will be bilingual measures of anticipated, day-to-day, and major discrimination validated for multiple health disparity populations using rigorous qualitative, quantitative, and mixed methods. Despite the high cognitive burden posed by discrimination measures, few studies have combined cognitive interviewing and psychometric approaches to validate them [85]. By subjecting these novel measures to a comprehensive and early evaluation of measurement equivalence, we will identify and be able to revise potentially problematic items before widespread use. Multiple studies have uncovered differential item functioning across diverse social groups among measures, such as the widely used Everyday Discrimination Scale [39,85,86], but only after they had been used in hundreds of studies [87] and were thus unlikely to be modified. The study will further advance measurement methods for health disparities research by determining the utility of including attributions in intersectional discrimination measures. If an attribution-free approach is viable, it will be possible to briefly assess discrimination experiences across a range of individual SSPs and their intersections in broad population surveys, enabling health disparities researchers to answer a much wider range of questions than with single-attribution measures.

### Limitations, Challenges, and Future Directions

Our 2-year study timeline is feasible because we have developed a two-stage analysis plan for cognitive interview data to ensure that any InDI revisions can be made rapidly, facilitating a timely launch of the quantitative survey. Our web-based recruitment and data collection plan will not be affected by social distancing requirements related to the COVID-19 pandemic. Nonrandom sampling will limit generalizability, but quota sampling will allow for the evaluation of InDI measures in intersectional strata that are typically small in representative surveys. The quantitative survey focuses on the largest racial and ethnic groups in the United States in which most health research on discrimination is conducted; as the design requires 1000 participants per racial or ethnic group, this restriction is necessary given finite resources. However, cognitive interviews will include all ethnoracial groups to ensure that revisions are made inclusively, and the qualitative findings will provide pilot data for future assessment of the InDI measures in other ethnoracial groups. Other future directions for this research include secondary use of the data (to be made publicly available) for intersectional analyses of relationships between discrimination and health among SGM persons of color, for whom large publicly available data sets are scarce.

## Appendix

Multimedia Appendix 1 Intersectional Discrimination Index test measures.

Multimedia Appendix 2 Peer-reviewer report from the Health Disparities and Equity Promotion Study Section, National Institutes of Health.

## Abbreviations

CAPTCHA: Completely Automated Public Turing test to tell Computers and Humans Apart
CFA: confirmatory factor analysis
InDI: Intersectional Discrimination Index
InDI-A: Intersectional Discrimination Index-anticipated
InDI-D: Intersectional Discrimination Index-day-to-day
InDI-M: Intersectional Discrimination Index-major
mCFA: multigroup confirmatory factor analysis
MIMIC: Multiple Indicator Multiple Cause
SGM: sexual and gender minority
SSP: social status and position
